### FINESSE AI–based risk reclassification framework (*Figure 2*)

To extend the predictive modelling framework described above, this study will implement a structured risk reclassification approach using FINESSE AI. This component is designed to translate model-derived risk estimates into clinically actionable categories and integrate them within existing diagnostic and management pathways.

**Figure 2 qyag143-F2:**
[figure not shown]
FINESSE—machine learning model development workflow.

Baseline risk for each patient will be defined using conventional clinical assessment and QRISK3 derived estimates, as previously described. FINESSE AI will then generate an updated, individualized probability of the outcome of interest at a specified time horizon by integrating echocardiographic parameters, haemodynamic response variables, clinical characteristics, and longitudinal data. The integrated risk estimate will be defined as:

$$R_{F}(i,t)=f(R_{0}(i,t),X_{e}(i),X_{h}(i),X_{c}(i),X_{l}(i))$$

where $R_{0}(i,t)$ represents the baseline risk estimate and the additional inputs correspond to echocardiographic, haemodynamic, clinical, and longitudinal variables, respectively.

To facilitate clinical interpretation, continuous risk estimates will be mapped to predefined categories using a threshold-based classification function. These thresholds will be prespecified and subsequently evaluated against observed event rates within the study cohort to ensure appropriate calibration defined as low risk–intermediate risk–high risk.

Risk reclassification will be defined as a change in category between baseline and FINESSE-derived estimates, expressed as the difference between the categorical assignments derived from $R_{F}(i,\;t)$ and $R_{0}(i,\;t)$. Reclassification will therefore reflect either upward or downward movement across predefined risk strata. To minimize clinically insignificant shifts, reclassification will only be considered when the absolute change in predicted risk exceeds a predefined threshold, anticipated to be in the range of 3–5 percentage points. The predefined 3–5% risk reclassification threshold was selected because it represents the range within which relatively small improvements in estimated cardiovascular risk may influence guideline-directed management decisions, including initiation or intensification of lipid-lowering therapy, additional diagnostic testing, or referral for invasive coronary angiography. Similar thresholds have been adopted in previous cardiovascular risk prediction studies evaluating improvements in discrimination and clinical utility through net reclassification analyses. The threshold was therefore chosen to maximize clinical relevance rather than statistical optimization alone.

In instances where FINESSE-derived risk estimates are discordant with conventional diagnostic findings, such as a low-risk SE profile in the presence of an elevated predicted risk, cases will be flagged for clinical review rather than automatically reassigned. This approach is intended to preserve alignment with established diagnostic pathways and ensure that model outputs are interpreted within the broader clinical context.

Rather than replacing current clinical assessment, the FINESSE framework is intended to function as a decision-support system embedded within routine SE reporting. Following completion of image interpretation, the algorithm automatically integrates demographic, clinical, laboratory, ECG and echocardiographic parameters to generate an individualized risk estimate. This risk estimate may assist clinicians in identifying patients who would benefit from intensified preventive therapy, further anatomical imaging, closer surveillance, or expedited invasive investigation while preserving final clinical judgement.

The incremental value of the FINESSE AI reclassification framework will be evaluated by comparing baseline and model-derived predictions using discrimination metrics, including the AUC, alongside calibration assessment using calibration plots and Brier scores. In addition, reclassification-specific metrics, including NRI and integrated discrimination improvement, will be used to quantify the extent to which FINESSE AI enhances patient stratification beyond conventional approaches.

### Ethics and dissemination

This study is conducted in accordance with the principles outlined in the *Declaration of Helsinki* and complies with all relevant UK regulatory and governance frameworks for health research. Ethical approval for the FINESSE project was obtained through the UK Health Research Authority (HRA) via the Integrated Research Application System (IRAS). The study received a favourable ethical opinion from the Yorkshire & The Humber—South Yorkshire Research Ethics Committee (REC) under REC reference: 19/YH/0159, with IRAS project ID: 249297. Subsequent protocol amendments, including version 6.1 (26 January 2022), were reviewed and approved with a favourable opinion by the same REC. All study procedures were therefore authorized to proceed in line with REC governance requirements.

In addition to REC approval, the study underwent review through the HRA approval process, ensuring compliance with NHS research governance, legal, and operational requirements across participating sites. Local approval was granted by the Milton Keynes University Hospital NHS Foundation Trust Research & Development (R&D) department (Protocol Record: MKUH-RD-008, Artificial Intelligence Stress Echo [FINESSE] Project).

Given the nature of the study, involving the use of routinely collected healthcare data and linkage with national datasets, additional regulatory approvals were required under UK data protection legislation. Approval for the use of confidential patient information without explicit consent was obtained from the Confidentiality Advisory Group (CAG) under HRA reference: 22/CAG/0034, following Section 251 of the NHS Act 2006. This approval permits the lawful processing and linkage of identifiable data where obtaining individual consent is not feasible, subject to strict safeguards.

Data linkage was conducted through secure NHS England data environments, following established governance pathways (DARS-NIC-662451-S5L8J-v0.16). Patient-level data from local NHS systems are pseudonymized prior to transfer and linkage with national datasets (e.g. mortality and hospital episode statistics). All data processing complies with the UK General Data Protection Regulation (UK GDPR) and the Data Protection Act 2018, with strict controls on access, storage, and data minimization. Only authorized personnel have access to de-identified datasets for analysis.

The FINESSE study is registered on ClinicalTrials.gov (Identifier: NCT07432620), ensuring transparency and public accessibility of the study protocol. Dissemination of results will occur through peer-reviewed publications, conference presentations, and engagement with clinical and academic stakeholders. Findings will be reported in accordance with relevant reporting guidelines (e.g. TRIPOD), ensuring reproducibility and transparency.

No individual participants will be identifiable in any dissemination outputs. Data sharing will follow institutional and regulatory policies, and any secondary use of data will require appropriate approvals.

### Confidentiality and access to data

The research team will anonymize patient data before securely storing it on institutional servers. Access to the dataset will be restricted to authorized research personnel only. Collaborative studies will operate under established data-sharing agreements that meet institutional and regulatory standards.

### Participant safety

This study is a retrospective observational analysis using routinely collected healthcare data and therefore poses minimal risk to participants. No direct patient contact, intervention, or alteration to clinical care is involved.

A waiver of informed consent was granted on the basis that the study uses existing data, involves no additional risk to participants, and that obtaining consent would be impracticable given the scale and retrospective nature of the dataset. The use of confidential patient information without explicit consent is supported by regulatory approvals under Section 251, with appropriate safeguards in place.

The primary potential risk relates to data confidentiality. This is mitigated through a structured data governance framework in which data are pseudonymized at source prior to transfer for research purposes. Identifiable information is not accessible to the research team. Data linkage with national datasets is performed within secure NHS data environments, using established processes that ensure separation of identifiers from clinical data. Access to data is restricted to authorized personnel only, with role-based permissions, secure storage, and full audit trails in place. All analyses are conducted on de-identified datasets, and results are reported in aggregate form to prevent re-identification of individuals. Given these safeguards and the non-interventional study design, no physical or psychological risks to participants are anticipated.

### Dissemination policy

The research findings will reach their audience through publications in peer-reviewed journals alongside conference presentations and institutional seminars. Clinicians will receive data-driven insights to support their decision-making processes in SE.

### Patient and public involvement

Patients and members of the public were not involved in the initial design of this retrospective study, as it is based on the analysis of pre-existing routinely collected clinical data. However, patient and public involvement (PPI) has been incorporated into the governance and oversight of the project. A dedicated PPI group contributed to the review and monitoring of the study’s data governance processes, particularly in relation to the use of confidential patient information without consent. This group provided input during the Confidentiality Advisory Group (CAG) approval process and has continued to offer oversight through regular follow-up and review meetings. Their role included ensuring that the use of patient data remained proportionate, transparent, and aligned with public expectations, as well as advising on communication and acceptability of data use.

While patients were not directly involved in defining the analytical methodology, their involvement has informed the ethical acceptability and accountability of the research.

This study represents an important step toward the responsible integration of machine learning into clinical practice, with ongoing commitment to strengthening patient-centred approaches in subsequent research phases.

### Expected outcomes

Development of a robust ML-based predictive model for adverse outcomes in SE. Identification of significant predictors, including echocardiographic, clinical, and demographic variables. Demonstration of the incremental value of ML over traditional statistical methods in improving diagnostic accuracy and risk stratification (*Figure 2*). Insight into the feasibility of integrating ML models into clinical workflows to personalize patient care and optimize resource utilization. (*Figure 2*).

### Patients characteristics & discussion

Quantitative machine learning performance analyses, including comparative AUC, NRI, integrated discrimination improvement, and calibration slope, will be reported in the primary results manuscript and have therefore been intentionally omitted from this protocol paper.

From the 2281 patients 14 patients’ data were excluded from analysis due to their indication for severity of aortic valve stenosis and viability only assessment in 8 and 6 patients respectively. As summarized in *Table 1*, of the 2267 patients undergoing dobutamine SE the median age was 63 years, 53% male, predominantly Caucasian race. Sixty-one percent had the diagnosis of hypertension, 59% dyslipidaemia, 30% diabetes mellitus, 10% current and 29% former smokers, and 10% obese (BMI≥30). The echocardiographic variables indicated 95% of the patients had preserved LVEF. During dobutamine SE 73% of patients achieved target HR (defined as 85% of the age predicted maximum HR), 16% had inducible myocardial wall motion abnormality, and 13% had biphasic response in keeping with viable and ischaemic response. Based on the number of inducible ischaemia of the 17 LV segments low-risk results (no inducible ischaemia) were present in 84%, intermediate-risk results (1–2 new RWMA) in 11%, and high-risk results (≥3 new RWMA) in 5% of cases. Patients with positive Dobutamine SE were more likely to be older males with traditional cardiovascular risk factors, particularly dyslipidaemia (64% vs. 59%, *P* = 0.031) and diabetes mellitus (34% vs. 29%, *P* = 0.036). They exhibited a higher burden of established disease, reflected by greater use of beta-blockers, ACE-I/ARB, anti-platelets, and nitrates, as well as higher QRISK3 scores (median 9.6 vs. 8. 1, *P* < 0.008). These findings align with established literature showing that male sex, dyslipidaemia, diabetes, and the use of cardiovascular medication predict inducible ischaemia on stress testing.^7,8^

Left ventricular systolic function was more frequently impaired in the positive group, with mild-to-moderate dysfunction (LVEF 36–49%) occurring in 7% vs. 3% (*P* = 0.005). During SE positive patients showed blunted chronotropic response (lower peak HR *P* = 0.018), albeit with no difference of the achieved target HR (70% vs. 73%, *P* = 0.21), consistent with higher beta-blocker use and possible underlying autonomic or myocardial dysfunction. The independent prognostic value of chronotropic incompetence during different forms of SE has recently been reported.^21,22^ As expected, peak and delta WMSI were significantly higher in the positive group.

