### Data collection

Data were collected using both SE reports and institutional EHR databases. Collected patient demographic information will include age, sex, race, height, weight, and body mass index. Cardiovascular risk factors such as; smoking habits, obesity status, family history of CAD, diabetes mellitus, essential hypertension, dyslipidaemia, prior CAD. Patients’ medical history at the time of the SE was also captured. Patients’ variables in support of calculating the QRISK-3 score^11^ was retrieved as complete as data permitted. (QRISK3 data extraction has been described in Supplement document). Extracted echocardiographic parameters include resting LV ejection fraction (from the WMS), and RWMA Wall Motion Score Index (WMSI) of the left ventricular 17 segments at each or the 4 stages of the SE protocol. (Detailed Dobutamine SE protocol and analysis is described in the Supplementary document.) To address inducible ischaemia the difference of the WMSI between low dose and peak stress of Dobutamine SE was calculated.^4,5^ Vital signs including systolic blood pressure (SBP), diastolic blood pressure (DBP), heart rate (HR) at rest and each stage of the SE protocol (low dose, peak stress, and recovery) were collected.

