### Sample size calculation

The study aims to include approximately 2300 patients undergoing SE for the assessment of inducible myocardial ischaemia. The sample size was determined based on anticipated event rates, longitudinal outcome modelling requirements, and the complexity of the proposed ML framework.

Previous SE studies and cardiovascular outcome registries suggest that MACE are expected to occur at sufficient frequency within long-term follow-up to support robust prognostic modelling.^12^ The projected cohort size is anticipated to provide an adequate number of outcome events to satisfy event-per-variable requirements for both conventional statistical analyses and ML-based predictive modelling, while reducing the risk of model overfitting. The proposed sample size is also considered sufficient to support internal cross-validation, subgroup analyses, calibration assessment, and the evaluation of multiple supervised ML approaches, including ensemble methods, support vector machines (SVMs), and neural networks. In addition, linkage with longitudinal NHS outcome datasets over extended follow-up periods is expected to strengthen survival modelling and time-to-event prediction analyses.

External validation using independent multicentre SE cohorts is planned to further assess model generalisability and robustness across different clinical settings.

*
Table 1
* shows the characteristics of the patient population.

**Table 1 qyag143-T1:** Population characteristics

Variable	Total	Positive SE	Negative SE	*P*-value
Anthropometric variables				
*N*	2263	371 (16%)	1892 (84%)	—
Age (years)	63 (55–72)	64 (57–72)	63 (54–72)	0.031
Male Sex	1201 (53%)	243 (65%)	958 (51%)	<0.0001
Race				
Caucasian	2048 (91%)	330 (89%)	1718 (91%)	0.42
Asian	152 (7%)	27 (7%)	125 (7%)	0.85
Black	39 (2%)	8 (2%)	31 (2%)	0.71
Other	24 (1%)	6 (2%)	18 (1%)	0.31
Height (cm)	167 (160–175)	168 (160–176)	167 (160–175)	0.285
Weight (kg)	80 (68–95)	82 (70–98)	79 (67–94)	0.009
BMI (kg/m^2^)	28.7 (24.8–33.5)	29.0 (25.1–33.9)	28.6 (24.7–33.4)	0.198
BSA (m^2^)	1.90 (1.75–2.08)	1.93 (1.78–2.11)	1.89 (1.74–2.07)	0.012
Cardiovascular risk factors factors				
Hypertension	1371 (61%)	240 (65%)	1131 (60%)	0.072
Dyslipidaemia	1345 (59%)	238 (64%)	1107 (59%)	0.031
Current Smoker	218 (10%)	44 (12%)	174 (9%)	0.092
Former Smoker	648 (29%)	114 (31%)	534 (28%)	0.285
Diabetes Mellitus	671 (30%)	127 (34%)	544 (29%)	0.036
Obesity (BMI ≥30)	232 (10%)	30 (8%)	202 (11%)	0.142

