Family History of CAD	996 (44%)	154 (42%)	842 (44%)	NS
Medications				
Beta-blockers	1122 (50%)	216 (58%)	906 (48%)	0.0003
ACE-I/ARB	1205 (53%)	233 (63%)	972 (51%)	<0.0001
Anti-platelets	1346 (59%)	260 (70%)	1086 (57%)	<0.0001
Statins	1320 (58%)	235 (63%)	1085 (57%)	0.028
DSE parameters				
Left Ventricular Ejection				
Fraction (rest)				0.005
Preserved (≥50%)	2153 (95%)	340 (92%)	1813 (96%)	
Mild/Moderate (36–49%)	83 (4%)	24 (7%)	59 (3%)	
Severe (≤35%)	24 (1%)	4 (1%)	20 (1%)	
HR at rest (bpm)	68 (60–77)	65 (58–74)	68 (60–78)	<0.001
HR at peak (bpm)	135 (120–147)	131 (115–144)	136 (122–148)	0.018
SBP rest (mmHg)	138 (125–153)	140 (127–156)	137 (124–152)	0.019
SBP peak (mmHg)	140 (118–160)	135 (112–155)	141 (120–162)	0.0110
DBP rest (mmHg)	80 (70–88)	81 (72–90)	79 (70–87)	0.042
DBP peak (mmHg)	70 (60–80)	68 (58–78)	71 (61–81)	0.011
THR achieved	1650 (73%)	260 (70%)	1390 (73%)	0.21
THR at peak (% of MTHR)	100 (90–110)	98 (85–108)	101 (91–111)	0.045
Double product (mmHg*bpm)	18 564 (15 820–21 330)	17 421 (14 650–20 268)	18 765 (16 093–21 560)	<0.001
Biphasic response (viable-ischaemic)	294 (13%)	59 (16%)	235 (12%)	0.072
WMSI at rest	1.05 (1.00–1.18)	1.12 (1.00–1.35)	1.00 (1.00–1.12)	<0.0001
WMSI at peak	1.06 (1.00–1.24)	1.18 (1.05–1.41)	1.00 (1.00–1.18)	<0.0001
Delta WMSI	0.00 (0.00–0.12)	0.05 (0.00–0.18)	0.00 (0.00–0.05)	<0.0001
Positive DSE (inducible ischaemia)	371 (16%)	371 (100%)	0 (0%)	—
Number of inducible ischaemic segments				
0	1896 (84%)	0 (0%)	1896 (100%)	—
1–2	250 (11%)	250 (67%)	0	—
3–4	100 (4%)	100 (27%)	0	—
≥5	21 (1%)	21 (6%)	0	—
QRISK3 score	8.4 (3.4–15.2)	9.6 (4.6–18.2)	8.1 (3.2–14.4)	0.008

Data are: Median (25–75 percentiles) for continuous variables, or *n* (%) for categorical variables. Left ventricular ejection fraction percentages are based on patients with categorized data (*n* = 2260; 21 missing/uncategorizable). Race approximated from ethnicity categories. Comparison by Mann–Whitney test for continuous variables and Chi-square test for categorical variables (for multi-category, overall test). *P* < 0.05 indicates statistical significance.

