### Stage 3: model evaluation, longitudinal risk prediction using NHS England (aka digital) data

In the final stage, the local Hospital dataset was linked with NHS England longitudinal records, which include confirmed cardiovascular events. The performance of ML score to predict clinical events will be evaluated against base models of QRISK3, and SE ischaemia positivity. The forecasting power of future cardiovascular events over 5-year and 10-year will be assessed.

This longitudinal modelling framework enables dynamic risk prediction and supports early identification of individuals at elevated risk of adverse cardiovascular outcomes. We will be inviting external sites for validation and testing the robustness and scalability of the developed predictive algorithm in all spectra of SE modalities.

Internal validation once completed external validation is performed using independent multicentre cohorts, including EVAREST and Stress Echo 2030 to assess generalisability of the model. Model discrimination will be assessed using the area under the receiver operating characteristic curve (AUC) with 95% confidence intervals (CIs). Calibration will be evaluated using calibration-in-the-large, calibration slope, observed-to-expected event ratios, calibration plots, and the Brier score. Where systematic miscalibration is identified, model recalibration using intercept and slope adjustment will be undertaken prior to assessing clinical utility by. using risk reclassification analyses, including the net reclassification improvement (NRI).

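### Table 1's SE-positivity label, ischaemic-segment count, biphasic flag and delta WMSI do not agree with one another, and SE positivity is a comparator for the ML score

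*Protocol article*

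**What the plan says.** The section Patients characteristics & discussion states that "16% had inducible myocardial wall motion abnormality, and 13% had biphasic response in keeping with viable and ischaemic response". Table 1 (printed under Sample size calculation) equates a positive test with inducible ischaemia: 371 in the positive column and none in the negative. Its segment-count rows place every SE-negative patient at zero inducible ischaemic segments. The biphasic row of the same table reads "Biphasic response (viable-ischaemic) 294 (13%) 59 (16%) 235 (12%) 0.072", in the order total, positive, negative and P-value.

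Data collection gives a further measure of ischaemia: "To address inducible ischaemia the difference of the WMSI between low dose and peak stress of Dobutamine SE was calculated". Table 1 reports delta WMSI, as median (25th–75th percentile), as 0.00 (0.00–0.12) overall, 0.05 (0.00–0.18) in positives and 0.00 (0.00–0.05) in negatives.

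Stage 3 then says that the ML score "will be evaluated against base models of QRISK3, and SE ischaemia positivity". On numbers, the Table 1 columns are 371 and 1892 of 2263, whereas the discussion speaks "of the 2267 patients undergoing dobutamine SE the median age was 63 years".

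**The concern.** Four descriptions of the same finding (label, segment count, biphasic flag, delta WMSI) should be explainable from one set of 17-segment, four-stage scores. As printed, a large group of patients labelled negative, with no ischaemic segment, has either a response that the text calls ischaemic or a rise in the index that the text uses to address ischaemia.

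The label is used beyond Table 1. It is one of two base models in Stage 3. The zero, 1–2 and 3-or-more segment groups supply the 84/11/5% SE risk strata in the discussion. The reclassification framework flags a low-risk SE profile that is discordant with a high predicted risk. The ML models receive WMSI across the stages (Data collection; Novelty and technical contribution). If the label leaves out ischaemia that those scores contain, part of the measured gain over SE positivity could come from repairing the label rather than from better prediction.

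**Working it through.** **1. Table 1's own figures.** 371 + 1892 = 2263 and 371/2263 = 16.4%, printed as 16%. 59 + 235 = 294 and 294/2263 = 13.0%, printed as 13%. 250 + 100 + 21 = 371, so the segment rows reproduce the number of positives. A chi-square test on 59/371 v 235/1892 gives P = 0.068 uncorrected and 0.082 with continuity correction; Fisher's exact test gives 0.076. The printed value is 0.072. None matches exactly, but all are close enough to suggest that the 59/235 split is what was analysed.

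**2. Biphasic flag against label.** 235/294 = 80% of biphasic responses are in the negative column. As a share of each column: 235/1892 = 12.4% of negatives and 59/371 = 15.9% of positives. If all 235 were counted as ischaemic, positivity would be (371 + 235)/2263 = 606/2263 = 26.8%. This is a sensitivity bound, not a corrected prevalence.

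**3. Delta WMSI against label.** I take delta as low dose to peak, as in Data collection, and assume that it is available for nearly all 2263 patients.
- An overall 75th percentile of 0.12 means that at least 0.25 × 2263 = 565.75, so 566 patients, are at about 0.12 or more.
- The median in 371 positives is the 186th ordered value, printed as 0.05. So at least 186 positives are at 0.05 or less, and at most 371 − 186 = 185 can be at 0.12 or more.
- Negatives at 0.12 or more: at least 566 − 185 = 381, and 381/1892 = 20.1%.
- Using the overall percentile alone, with all 371 positives placed at 0.12 or more, at least 566 − 371 = 195 negatives remain.
- At most 235 negatives are biphasic, so at least 381 − 235 = 146 of the 381 are not.

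On 17 segments one grade is 1/17 = 0.059 and two grades are 2/17 = 0.118, so 0.12 is about two segment-grades.

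**4. Is the delta row itself plausible?** The printed 0.05 (positive median and negative 75th percentile) is not a multiple of 1/17. Rounding 0.059 gives 0.06. Truncating it gives 0.05, but then 0.118 would print as 0.11, not 0.12. The negative 75th percentile of 0.05 allows at most 0.25 × 1892 = 473 negatives above 0.05, and step 3 needs 381 of them (381/473 = 81%) at 0.12 or more. That is possible but strained.

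**5. Counts.** 1896 + 250 + 100 + 21 = 2267 = 2281 − 14, which agrees with the discussion but not with the column total of 2263. The zero-segment row shows 1896 as 100% of a column of 1892. The four extra patients are all in that row.

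**The case against.** The strongest reply is that a table of disagreeing measures does not show that the label is the faulty one.

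- **Positives with delta 0.00.** The 25th percentile of 0.00 means that at least 93 positives (0.25 × 371 = 92.75) have no net rise. This is not a contradiction. An abnormality already present at low dose and unchanged at peak, or seen only in recovery, gives zero. WMSI is an average, so improvement in one segment can also offset worsening in another. This objection stands, and these patients are not counted here.
- **Negatives with a rise.** The discussion counts new wall motion abnormalities. A segment abnormal at rest that improves at low dose and then worsens again could raise delta, and be called biphasic, without counting as new. This could explain part of both the 235 and the 381, which overlap. It is numerically possible, since the negative 75th percentile of resting WMSI is 1.12 and so at least 473 negatives are at or above that value. But at least 146 of the 381 are not flagged biphasic. A net rise needs at least one segment to worsen between low dose and peak, and Table 1 heads the row as inducible ischaemic segments rather than new abnormalities. The explanation may be right, but the article does not give it. The detailed SE protocol is in a supplement that is not shown.
- **The delta row may be misprinted.** This is fair. A lower overall 75th percentile would shrink or remove the 381. The biphasic split does not depend on that row.
- **Effect on results.** Outcomes come from NHS England linkage, so the label does not contaminate the endpoint. Extracting more from stage-wise WMSI than a yes/no label offers is also a declared aim. Both points stand: an inflated gain is a risk, not a demonstrated artefact.

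A reader might infer that hundreds of patients are misclassified, or that true positivity is 26.8%. The documents support neither inference, because they do not say which measure is wrong.

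**Conclusion.** The point holds as an inconsistency in what is reported. The firmest part is that 235 SE-negative patients (12.4% of negatives), all with zero ischaemic segments recorded, carry a response that the text calls viable and ischaemic. The second part is conditional: at least 381 negatives (about 20%) with a rise of about 0.12 or more, at least 146 of them not biphasic. It rests on the printed percentiles being right, on near-complete delta data, and on delta being low dose to peak. The count mismatch is certain but small: four patients, 2263 against 2267 and 1892 against 1896.

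Misclassification of the label is possible but not proven. The consequence is that a stated comparator lacks a definition consistent with the study's other ischaemia measures, so a gain over it could not be cleanly interpreted.

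**What to change.** Before models are compared:

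1. Re-derive the ischaemic-segment count, biphasic flag and delta WMSI for every patient from the stored 17-segment, four-stage scores with one written algorithm. Check each against the recorded positivity label. This is a check and need not replace a clinical read as the comparator.
2. Reconcile Data collection, Table 1 and Patients characteristics & discussion on what counts as inducible ischaemia, including how biphasic responses and segments abnormal at rest are handled. Which rule to adopt is for the investigators.
3. Correct the 2263/2267 and 1892/1896 counts and any wrong delta WMSI percentiles.
4. Use the same definition in the external cohorts where their data allow.
5. Report the comparison with SE positivity with the biphasic negatives counted once as negative and once as positive, as a sensitivity analysis.

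The cost is a small amount of scripted work on data already extracted, and possibly changed Table 1 figures. The article says that the ML performance results are still to be reported, so the check can precede them.
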